**LIST OF ABBREVIATIONS AND RELEVANT DEFINITIONS**

|                |                                                                                                                                                                                                                                                                                                                                                  |
|----------------|--------------------------------------------------------------------------------------------------------------------------------------------------------------------------------------------------------------------------------------------------------------------------------------------------------------------------------------------------|
| ABR     | General Assessment and Registration form (ABR form), the application form that is required for submission to the accredited Ethics Committee; in Dutch: Algemeen Beoordelings- en Registratieformulier (ABR-formulier)                                                                                                                    |
| AE      | Adverse Event                                                                                                                                                                                                                                                                                                                             |
| AR      | Adverse Reaction                                                                                                                                                                                                                                                                                                                          |
| CA      | Competent Authority                                                                                                                                                                                                                                                                                                                       |
| CCMO    | Central Committee on Research Involving Human Subjects; in Dutch: Centrale Commissie Mensgebonden Onderzoek                                                                                                                                                                                                                               |
| CV      | Curriculum Vitae                                                                                                                                                                                                                                                                                                                          |
| DSMB    | Data Safety Monitoring Board                                                                                                                                                                                                                                                                                                              |
| EU      | European Union                                                                                                                                                                                                                                                                                                                            |
| EudraCT | European drug regulatory affairs Clinical Trials                                                                                                                                                                                                                                                                                          |
| GCP     | Good Clinical Practice                                                                                                                                                                                                                                                                                                                    |
| GDPR    | General Data Protection Regulation; in Dutch: Algemene Verordening Gegevensbescherming (AVG)                                                                                                                                                                                                                                              |
| IB      | Investigator's Brochure                                                                                                                                                                                                                                                                                                                   |
| IC      | Informed Consent                                                                                                                                                                                                                                                                                                                          |
| IMP     | Investigational Medicinal Product                                                                                                                                                                                                                                                                                                         |
| IMPD    | Investigational Medicinal Product Dossier                                                                                                                                                                                                                                                                                                 |
| METC    | Medical research ethics committee (MREC); in Dutch: medisch-ethische toetsingscommissie (METC)                                                                                                                                                                                                                                            |
| POSAS   | Patient and Observer Scar Assessment Scale                                                                                                                                                                                                                                                                                                |
| (S)AE   | (Serious) Adverse Event                                                                                                                                                                                                                                                                                                                   |
| SPC     | Summary of Product Characteristics; in Dutch: officiële productinformatie IB1-tekst                                                                                                                                                                                                                                                       |
| Sponsor | The sponsor is the party that commissions the organisation or performance of the research, for example a pharmaceutical company, academic hospital, scientific organisation or investigator. A party that provides funding for a study but does not commission it is not regarded as the sponsor, but referred to as a subsidising party. |
| SSG     | Split thickness skin graft                                                                                                                                                                                                                                                                                                                |
| SUSAR   | Suspected Unexpected Serious Adverse Reaction                                                                                                                                                                                                                                                                                             |
| TBSA    | Total Burned Surface Area                                                                                                                                                                                                                                                                                                                 |
| UAVG    | Dutch Act on Implementation of the General Data Protection Regulation; in Dutch: Uitvoeringswet AVG                                                                                                                                                                                                                                       |

**WMO**      **Medical Research Involving Human Subjects Act; in Dutch: Wet Medisch-wetenschappelijk Onderzoek met Mensen**

## SUMMARY

**Rationale:** Deep dermal / sub dermal (burn) wounds need surgical excision followed by skin grafting to achieve rapid wound healing. Most common method is split thickness skin grafting (SSG). However, in extended (burn) wounds there is a lack of donorsite to harvest skin transplants. Moreover, regarding donorsite morbidity it is always high priority to keep donorsite as small as possible. For these reasons, skin grafts are often expanded before application on the wound. Skin graft expansion is generally performed by meshed skin grafting technique, seen this method is considered to be quick and easily applicable. Yet, this technique also has several limitations. For the surgeon this method becomes more cumbersome when the expansion ratio increases. Moreover, the actual expansion of the skin graft is usually lower than the intended expansion ratio and the "fish-net" pattern often stays visible in the eventual scar. An alternative for skin graft expansion is the micrografting technique (Meek technique). In comparison with meshed skin grafting this technique is able to reach true large expansion ratios and thereby maintain small donorsites. As a consequence, this technique is used in particular for very extended (burn) wounds. Both expansion methods are used worldwide in specialized burn centers. Wound healing seems to be similar according to previous published literature. Experience shows a possible advantage of micrografting on scar quality. Three studies compared these two expansion techniques, however none primarily investigated possible differences within long-term scar quality in a prospective study setting. To compare long-term scar quality of micro-versus mesh grafting techniques in deep/subdermal (burn) wounds and thereby providing evidence for the use of micrografting not only for extensive but also for smaller (burn) wounds a randomized controlled trial is highly preferred.

**Objective:** To assess long-term scar quality and donorsite size of deep dermal or sub dermal (burn) wounds after skin grafting with micrografting compared to mesh grafting technique.

**Study design:** Multicenter randomized intra-patient controlled trial.

**Study population:** All adult patients with (burn) wounds affecting 4 - 20% total body surface area with an indication for surgical excision and skin grafting, admitted to the burn center at the Red Cross Hospital in Beverwijk, Netherlands or the burn center of the University Hospital Ghent, Belgium.

**Intervention:** Prior to surgery two comparable (burn) wounds or two equal parts in one (burn) with a minimum size of 36 cm^2 will be selected. These wounds will be randomly allocated to the intervention group (micrografting) or the comparison group (meshed skin grafting).

**Main study parameters/endpoints:** The main study parameter is scar quality 12 months after either skin grafting. Possible differences in scar quality between both techniques observed by means of Patient and Observer Scar Assessment Scale (POSAS).

**Nature and extent of the burden and risks associated with participation, benefit and group relatedness:** All patients will have to undergo surgery, independent of skin grafting method. Seen both skin grafting techniques are already been considered as standard treatments, there is no additional risk micrografting compared to meshed skin grafting. The only risk concerns a possible subtle asymmetry of the scar due to two different grafting techniques. However, in practice both techniques are also being combined within one patient. Follow-up broadly corresponds with standard follow-up for (burn) wounds. The duration of check-up at outpatient clinic is slightly increased to 60 minutes, due to additional examinations and surveys.

## 1. INTRODUCTION AND RATIONALE

Patients with deep dermal burns or full thickness wounds always require a surgical reconstruction with skin grafts to restore the integrity of the outer skin layer. Most of the deep burn wounds are covered with split thickness skin grafts (SSG) which is the standard of care (SOC) treatment nowadays. However, in order to achieve rapid wound closure in extensively burned patients, the shortage of available donor areas for skin graft harvesting represents a significant problem. As a result, coverage of the majority of burn wounds or full-thickness skin defects unavoidably requires an expansion of the skin graft before application.

Currently there are two distinct methods for skin graft expansion. The most frequently used technique worldwide is the easy and fast meshed graft technique whereby the skin theoretically can be enlarged 1.5 to 9 times. The larger the expansion rate, the less donor skin is needed. Unfortunately, it has been demonstrated that in reality the claimed expansion ratios are never achieved with meshed grafts whereby e.g. a 1:3 expansion only results in about 60% increase in size. Therefore, even more donor skin or even larger expansion ratios are needed in order to cover all wounds in severely burned patients. Various additional problems arise due to the use of widely meshed skin grafts, both for the patient and for the surgeon. Mesh-expanded skin grafts take much longer to completely epithelialize and often result in hypertrophic scar formation and contractures. Moreover, in the long-term, a lasting “fishnet or string-vest” pattern will always be visible in meshed grafted areas. An additional technical problem is that skin grafts that are meshed with a ratio above 1:3 are fragile and very difficult to handle for the surgeon.

The second, also currently used method for skin graft expansion is the micrografting technique. It was mainly the need for more manageable and larger expansion ratios in order to increase the survival rate in extensively burned patients that has led to the development of the more labour- and material intensive micrografting technique. With this method, a much more effective expansion of the skin grafts can be achieved, more equal to the claimed expansion ratios resulting in a smaller donor site area. The micrografting technique has been established in many (usually more specialized) burn centers throughout the world due to the easier handling and the lower fragility compared to the widely meshed skin grafts which can be of particular benefit for very extensive burns. For all these reasons, in most burn centers, the micrografting technique is only recommended and reserved for severe burns with at least more than 30-40 % total burned surface area (TBSA).

In addition, and independent of the expansion method, it is important to mention that donor site morbidity actually is an often seriously underestimated problem which in the short term frequently causes the patient more pain than the actual burn.

Since many years, the meshed skin graft technique and the micrografting technique are routinely used (combined) both in Belgium and The Netherlands, therefore providing a true reflection of the current clinical practice. In our burn center extensively (>30%) burned patients are (mostly) treated with the micrografting technique in order to save as much donor site area as possible. During follow-up of many of these patients we often noted a surprisingly good quality of the residual scars following the application of micrografts.

The increased interest in obtaining a good functional and aesthetic outcome after burn surgery is an illustration of the current paradigm shift in burn management from a focus solely on survival towards the overall quality of survival which is often related to the residual scars of the burn patients.

With this in mind and due to the good results obtained in extensively burned patients we started about 6 years ago to use the micrografting technique in much smaller burns. Our clinical experience showed that the initial graft take as well as scar quality were excellent and donorsite morbidity was substantially reduced. These results together with fact that scar quality of meshed graft technique and micrografting technique has never been prospectively to each other, prompted us to compare this within an adequately developed study.

This study involves a large (intra-individual) randomized controlled trial in a multicenter setting to evaluate the effect of two skin grafting techniques both on the quality of scar formation and the reduction of donor site morbidity. This study is crucial in order to provide evidence for a more widespread use of the micrografting technique and this not only for extensively burned patients but also for smaller burns in need of skin graft expansion. All relevant outcome parameters will be evaluated during acute phase and the follow-up period of 12 months.

Our hypothesis is that treatment with micrografting, when compared to conventional meshed skin grafting, will result in a better scar quality and smaller donorsite size.

## 2. OBJECTIVES

### Primary Objective:

- To assess long-term scar quality of deep dermal or sub dermal (burn) wounds after skin grafting with micrografting compared to mesh grafting technique.

### Secondary Objectives:

- To assess donorsite morbidity, wound healing, epithelisation, mobility and quality of life after skin grafting with micrografting versus mesh grafting.

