### 4.3 Exclusion criteria

- Patient has participated in another study utilizing an investigational drug or device within the previous 30 days
- Wounds covering face, hands or joints
- Patient has one or more medical condition(s) that in the opinion of the treating physician would make the patient an inappropriate candidate for this study
- Patients who are expected (according to the responsible medical doctor) to be non-compliant to the study protocol. (This includes patients with severe cognitive dysfunction/impairment and severe psychiatric disorders).

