#### 8.1.2 Secondary study parameters/endpoints (if applicable)

- Long-term scar quality 3 and 12 months after skin transplantation
  - Subjective measurement of scar quality with Patient and Observer Scar Assessment Scale (POSAS). This is based on multiple aspects of scar formation such as: vascularization, pigmentation, texture, thickness, pliability, itch and pain, and is performed by member of research team and by patient.
  - Objective measurements of scar color and pigmentation with the Mexameter or Dermaspectrometer. Skin elasticity is objectively measured with the Cutometer.
- Skin graft technique preferred by patient
  - Patient gives overall indication as to what skin graft technique he/she would prefer if he/she were to require skin grafting again: weekly during admission, and at 3 and 12 months follow up
- Donorsite size and ratio of donorsite size and actual graft size (cm^2)
  - Surface areas will be calculated with a 3D-camera (Woundworks inSight)
- Take rate of skin grafts
  - Take rate will be clinically assessed at 8 +/- 2 days and expressed as the percentage of micrografted and meshed graft take
- Healing time
  - Clinical assessment of wound healing 14 and 21 days +/- 2 post application expressed as percentage of the total wound surface area healed
  - Time to complete wound closure where complete wound closure is defined as > 95% re-epithelialization of the wound with the absence of drainage and no longer needing a substantial wound dressing
- Bacterial load
  - Wound swabs for semi-quantitative investigation
  - Semi-quantitative bacteriology in both groups
  - Percentage of patients within both groups with clinical wound infection requiring systemic antimicrobial therapy
  - 'Clinical infection' is defined as the presence of cellulitis and/or visible purulence and/or lymphangitis combined with one or more of the following: local wound pain/erythema/edema/malodor

- Pain
  - Will be evaluated in the autografted target wounds with help of a Visual Analogue Scale (VAS score) on day 2 post surgery, before and after removal of Surfasoft®/Urgotul in case of meshed skin grafts or plissees in case of micrografting, and thereafter once weekly during the hospitalization period. After hospital discharge pain will be evaluated again at the 3 and 12 months follow ups
- Number of secondary procedures
  - Re-interventions in study areas due to insufficient take or necessity of reconstructive surgery
- Mobility at 3 and 12 months

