  - If articulations of limbs are involved the Quick Dash for upper extremities and the Lower extremity functional scale for lower extremities, the range of motion will be assessed with a goniometer
- Quality of life
  - Assessed at the time of hospital discharge and at 3 and 12 months after the procedure. 3 quality of life measures, the EQ5D-5L, SF36 and DLQI will be used at different points in time: at the time of hospital discharge and 3 and 12 months post wound healing
- Health economics
  - Differences in operation time, costs of materials/equipment used and staff/personnel and impact of re-interventions and the need for reconstructive surgery will be evaluated. Using regression analysis based on the processing of the EQ5D-5L, SF36 and the DLQI we will be able to construct an economic model. The model will incorporate the short-term costs involved of both skin expansion techniques as well as the long-term costs.
- Incidence of AE and SAE
  - There are no Adverse Events (AEs) expected, relating to this study (comparison of two already practiced skin grafting techniques).
  - A Serious Adverse Event (SAE) is any untoward medical occurrence in a subject who is participating in a clinical study performed. This is defined as an event that is:
    - a) fatal
    - b) life-threatening
    - c) requires or prolongs inpatient (unexpected) hospitalization
  - These SAEs will be reported directly to the METc.
  - SAEs related to surgical treatment in general will be noted in a line-listing and will be reported yearly to the METc. These are defined as an event that results in a:
    - a) pneumonia
    - b) urinary tract infections
    - c) sepsis

- d) pulmonary embolism
- e) re-operation

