## 8.2 Randomisation, blinding and treatment allocation

Randomization will be at intra-patient level and performed by means of the Redcap randomization module (most often 5-7 days post allograft application). Preferably 2 wounds in the same patient will be randomized, or alternatively, after discussing this situation with the patient, 1 wound will be divided into 2 halves (A and B). The sequence in which the micrografting and mesh grafting techniques will be applied will also be subject to randomization by means of the Redcap randomization module. In surgical treatment blinding is not possible, as the burn surgeon knows which part of the wound receives what surgical treatment. Outcome assessment will be blinded as the junior investigator/research nurse who does the follow-up measurements is unaware of the technique used in target wound A or B.

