### **10.2 Secondary study parameter(s)**

All continuous data will be assessed with a paired student's t-test, or when data are not normally distributed with a Wilcoxon signed-rank test.

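### Every patient receives both techniques, so the quality-of-life and mobility questionnaires cannot compare them; the infection endpoint needs restating per wound

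*Protocol*

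**What the plan says.** Section 8.2 sets the unit of randomisation: "Randomization will be at intra-patient level and performed by means of the Redcap randomization module". Two wounds in one patient are preferred; otherwise "1 wound will be divided into 2 halves (A and B". No patient receives only one technique.

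Section 2 gives one secondary objective, framed as a contrast of techniques: "To assess donorsite morbidity, wound healing, epithelisation, mobility and quality of life after skin grafting with micrografting versus mesh grafting".

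Section 8.1.2 lists the measures:
- Quality of life: EQ5D-5L, SF36 and DLQI, listed by time point, with no per-wound form.
- Mobility: "If articulations of limbs are involved the Quick Dash for upper extremities", LEFS for the lower limb, and goniometer range of motion.
- Health economics: differences in operation time, materials, staff and re-interventions, and then "Using regression analysis based on the processing of the EQ5D-5L, SF36 and the DLQI we will be able to construct an economic model".
- Infection: "Percentage of patients within both groups with clinical wound infection requiring systemic antimicrobial therapy". Clinical infection itself is defined by local signs at the wound.

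Section 10.2 sends all of the continuous measures to one kind of test: "All continuous data will be assessed with a paired" t-test, or the Wilcoxon signed-rank test if the data are not normal. Section 4.3 excludes "Wounds covering face, hands or joints".

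**The concern.** A within-patient design gains its precision by comparing two wounds in the same person. That works only for outcomes that take a separate value for each wound. A questionnaire about the person's health, skin-related quality of life or limb function takes one value, and that value follows from both grafts together and from the rest of the burn.

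The objective in Section 2 promises a technique comparison on such scores, and Section 10.2 names a test that needs two values per patient. An analyst who follows the text has either a test that cannot be run or an unplanned substitute, such as change over time, which says nothing about technique. Any technique effect reported on quality of life would come from modelling assumptions while carrying the authority of a randomised trial. The infection endpoint has a milder form of the same fault: its wording counts patients, although the things allocated are wounds.

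**Working it through.** **1. Where the pairing works.** The sample-size figures in Section 4.4 rest on wound-level pairs, and they reproduce.

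- POSAS: SD of the paired difference = √(2 × 2.4² × (1 − 0.5)) = 2.4. With a mean difference of 1, two-sided alpha 0.05 and the noncentral t distribution on n − 1 degrees of freedom, 48 pairs give power 0.807 and 63 pairs give 0.902, as stated. Then 63 / (1 − 0.10) = 70 patients, as stated.
- Donor site: SD on the log scale = √(ln(1 + 0.09²) + ln(1 + 0.03²)) = √(0.00807 + 0.00090) = 0.0947. A ratio of 1.1 with 13 pairs gives power 0.914, and a ratio of 1.2 with 6 pairs gives 0.960, both as stated. Then 6 / 0.90 = 6.67, rounded up to 7.

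**2. Where it fails.** For a wound-level outcome, write the value for patient i under technique j as Y(i,j) = a(i) + t(j) + e(i,j). The paired difference removes a(i) and leaves t(micro) − t(mesh) plus noise, so the technique effect can be estimated.

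A whole-patient score is a single value Q(i), observed under exposure to both techniques. The technique indicator does not vary between patients or within them. Entering Q(i) under both techniques gives d(i) = Q(i) − Q(i) = 0 for every patient, with mean 0 and SD 0. The t statistic is 0/0, and the signed-rank test has no non-zero differences to rank. Patients contributing a contrast: 0 of 70. More patients would not change this.

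Two routes around this do not help. Regressing the score on the area grafted by each technique fails because the Summary asks for comparable wounds or equal parts; the share is close to constant by design, and what variation remains is not randomised. A patient with one target wound on an arm and one on a leg would have a Quick DASH and a LEFS, but these are different scales and not a pair.

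**3. Secondary outcomes by unit.**

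| Outcome (Section 8.1.2) | Unit of the value | Technique contrast? |
|---|---|---|
| EQ5D-5L, SF36, DLQI | Patient | No |
| Quick DASH, LEFS | Patient | No |
| Regression on EQ5D-5L, SF36, DLQI | Patient | No randomised difference |
| Operation time, materials, staff, re-interventions | Can be recorded per wound | Yes |
| Clinical infection (local signs) | Wound | Yes, if scored per wound |
| Systemic antimicrobial therapy | Patient | No |
| Range of motion | Joint or limb | Only if target wounds lie on separate limbs |

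**4. Mobility and eligibility.** Section 8.1.2 calls for mobility assessment when limb joints are involved, while Section 4.3 excludes wounds over joints. If the exclusion concerns target wounds only, mobility would reflect other burns, which are still less attributable to the randomised technique. If it concerns the patient, few or none would qualify. The text does not say which is meant.

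**The case against.** The strongest reply is that the fault is narrower than it looks, and much of that reply stands.

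- **Infection.** A reader might infer that the trial cannot compare techniques on infection at all. The documents do not support that. Section 8.1.2 defines clinical infection by local signs, Section 8.3 takes swabs from each target wound, and the Summary uses the word group for allocated wounds. An infection can be assigned to wound A or B; only the systemic treatment is shared.
- **Mobility.** A reader might infer that the whole mobility objective is lost. Range of motion is measured per joint or limb and can be compared where the two target wounds lie on different limbs. The Protocol does not require that and allows halves of one wound, so the subset may be small, but it need not be empty.
- **Economics.** A reader might infer a failed cost-utility analysis. The Protocol never states an incremental-utility or cost-per-utility claim. It describes a regression based on the questionnaires, without giving its form, beside costs that can be recorded per technique. An analysis plan may specify the model. It cannot create a second questionnaire score per patient, so that part still lacks a randomised difference.
- **Joint exclusion.** This is a matter of consistency between two sections, separate from the unit of analysis.
- **Weight.** The hypothesis in Section 1 concerns scar quality and donor-site size, not quality of life or mobility.

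None of this rescues the five questionnaires. The contradiction lies in the Protocol's own objective and test, so it is not a detail left to the analysis plan.

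**Conclusion.** The point holds for EQ5D-5L, SF36, DLQI, Quick DASH and LEFS: no estimable difference between techniques at any sample size, against an objective and a test that presuppose one. It carries over to the part of the economic model built on three of those instruments. The infection endpoint is mis-specified but can be repaired. Range of motion is comparable in a limited subset.

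This rests on one assumption: each questionnaire is completed once per patient per visit. The Protocol describes no per-wound version of any of them.

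It would be wrong to conclude that the design is invalid or that the secondary outcomes fail as a whole. POSAS at 12 months, its paired test and the 63 pairs inflated to 70 patients are untouched, as are the other outcomes measured per wound. The correction is a should-fix to secondary outcomes.

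**What to change.** 1. **Sections 2 and 10.2.** Reword the objective so that quality of life and the mobility questionnaires are described for the whole cohort, without a technique contrast, and exempt these five instruments from the paired test.
2. **Section 8.1.2, health economics.** Limit the between-technique comparison to items recorded per target wound (operation time, materials, staff, re-interventions). Use the questionnaires descriptively only. The form of the cost model can otherwise stay the sponsor's choice.
3. **Section 8.1.2, infection.** Score clinical infection separately for target wounds A and B, compare as paired proportions, and report systemic antimicrobial therapy once per patient.
4. **Sections 8.1.2 and 4.3, mobility.** Compare range of motion between techniques only where the target wounds lie on separate limbs. Reconcile the mobility endpoint with the exclusion of wounds covering joints, stating whether the exclusion applies to target wounds or to the patient.

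The cost is a change of wording, plus recording cost items and infection signs per target wound. No extra patients, visits or questionnaires are needed. The sponsor gives up a technique claim on quality of life, which these data could not have supported.
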